## Abstract

**Background:**

Pleural lavage is regularly performed before closing the chest wall in pulmonary surgeries to prevent pleural implantation of tumor cells and postoperative infection. However, scant data could be found in the literature regarding the optimal regimen for performing pleural lavage. To establish a proper volume of pleural lavage, we herein designed a protocol for a randomized controlled trial.

**Methods:**

A total of 400 participants with non-small cell lung cancer undergoing video-assisted thoracoscopic surgery (VATS) lobectomy and systematic mediastinal lymph node dissection (MLND) will be randomly assigned to one of two groups: group A (500 mL pleural lavage fluid) and group B (3000 mL pleural lavage fluid). The primary outcomes include the levels of leukocytes, neutrophils, and inflammatory factors on the first postoperative day. The secondary outcomes include (i) the levels of leukocytes, neutrophils, and inflammatory factors on the second and third postoperative days; (ii) the incidence of postoperative fever on the first, second, and third postoperative days; (iii) the volumes of chest drainage within the first 3 operative days, the duration of drainage, and postoperative hospitalization; and (iv) the incidence of postoperative complications (incision infection, pain, atelectasis, hemorrhage, etc.) and the incidence of pleural effusion requiring thoracic puncture or drainage within 30 days after surgery. The main content of the analysis includes effectiveness and safety analysis. We will perform subgroup analyses to identify potential influence factors.

**Discussion:**

As far as we know, this will be the first randomized controlled trial to compare the clinical outcomes between different volumes of pleural lavage fluid following VATS and MLND. Findings from this trial will determine the appropriate amount of pleural lavage before chest wall closure.

**Trial registration:**

This study was registered with the Chinese Clinical Trial Registry ( on 17 March 2019. ChiCTR 1900021950).

## Background

In pulmonary surgery, pleural lavage is routinely performed before closing the chest wall, to rinse off residual tumor cells and tissues and ideally prevent pleural implantation of tumor and postoperative infection [1]. Decades ago, it was known that even if there were no obvious malignant pleural effusion or pleural implants, tumor cells could be found in as much a third of postoperative pleural lavage [2]. Since then, accumulating data have indicated the presence of tumor cells in intraoperative pleural lavage as an independent prognostic factor [3–5]. Intraoperative pleural lavage cytology detected before closure could present a higher prognostic value than pleural lavage cytology detected before thoracotomy. Furthermore, it could guide the choice of adjuvant chemotherapy for lung cancer patients after surgery.

Although there is no guideline regarding how pleural lavage should be conducted [6], usually it involves irrigating the thoracic cavity with 0.9% sodium chloride injection varying from 20 to 2000 mL [2, 7–9] at 38~40 °C [10]. However, there are no determinant criteria on the volume of pleural lavage fluid. If the volume of pleural lavage is too small, the residual tumor cells and tissue cannot be washed away, which may result in increased absorption of inflammatory mediators, fevers, and even severe inflammatory reactions [11]. It could affect prognosis and prolong hospitalization [12]. Furthermore, the residual tumor cells may increase the risk of recurrence [13] and metastasis [14–16]. If the volume of pleural lavage is excessive, it will cause waste of resources and prolongation of operation time. Kaneda et al. [9] found that doses of over 500 mL could cause false-negative results of pleural lavage cytology. Considering clinical practice and the literature [7, 8], we decided to test two volumes of pleural lavage: 500 and 3000 mL.

We will prospectively enroll non-small cell lung cancer (NSCLC) patients undergoing video-assisted thoracoscopic surgery (VATS) for lobectomy and systematic mediastinal lymph node dissection (MLND). After enrollment, we will randomly allocate patients to one of two groups: group A (500 mL pleural lavage fluid) or group B (3000 mL pleural lavage fluid). Blood samples will be collected to test for leukocytes, neutrophils, and inflammatory factors. Postoperative complications, the volume of pleural drainage, and length of hospital stay will also be recorded. We aim to compare the clinical benefits for patients with NSCLC between different volumes of pleural lavage fluid following VATS lobectomy and MLND.

## Methods/Design

### Trial design

This is a single-blind, single-center, randomized controlled trial (Fig. 1). This study protocol adheres to the Standard Protocol Items: Recommendation for Interventional Trials (SPIRIT) statement. The SPIRIT figure (Fig. 2) summarizes the items of enrollment, intervention, and follow-up. The detailed SPIRIT checklist is also provided (Additional file 1).

**Fig. 1 Fig1:**
[figure not shown]
Standard Protocol Items: Recommendation for Interventional Trials (SPIRIT) figure

**Fig. 2 Fig2:**
[figure not shown]
Flowchart for participants’ identification, assessment, enrollment, randomization, intervention, and follow-up

### Study objective

This study aims to identify the effects of different volumes of pleural lavage fluid on perioperative outcomes of patients with NSCLC following VATS lobectomy and MLND.

### Study location

This study will be conducted in NSCLC patients undergoing VATS lobectomy and MLND in the Department of Thoracic Surgery, West China Hospital, Sichuan University.

### Recruitment

#### Recruitment of participants

Patients eligible for this trial must comply with all the inclusion criteria and must not meet any exclusion criteria. To achieve adequate enrollment, all surgeons in the thoracic department of the hospital are informed of this trial. Each included patient will sign an informed consent form. The consent form includes (i) the detailed explanation of the study design, including backgrounds and aims of this trial; (ii) the benefits and risks of participating; and (iii) the strategy and compensation for the participants if they experience any harm as a result of trial participation.

#### Inclusion criteria

Patients who meet all the following criteria at the start of the treatment are eligible for this study: (i) patients between 18 and 75 years of age, (ii) patients undergoing planned VATS lobectomy and MLND, (iii) be American Society of Anesthesiologists grade I or II, (iv) essential materials such as clinical staging of lung cancer and medication were complete, (v) confirmed diagnosis of NSCLC through pathological examination after surgery, and (vi) willing to participate after reading and signing an informed consent form.

#### Exclusion criteria

Patients who meet any of the following criteria at the start of treatment are excluded from this study: (i) last smoked fewer than 2 weeks prior to surgery for current smokers, (ii) preoperative hydrothorax of patients was predominant, (iii) patients were pregnant or breastfeeding (females from 18 to 55 years of age should receive a pregnancy test), (iv) patients with preoperative severe mental illness, (v) patients with preoperative gastrointestinal or blood system disease, (vi) patients underwent cardiac ischemia, (vii) patients receiving preoperative radiotherapy or neoadjuvant chemotherapy, (viii) intraoperative accidents such as hemorrhage (>500 mL), conversion to open surgery, or cardiac arrest happened to the patients, and (ix) patients with severe postoperative bleeding or persistent air leakage, which require reoperations.

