### Randomization and blinding

Randomization of trial participants will be based on computer-generated random numbers prior to surgery. The random numbers will be printed and placed in consecutively numbered and separate sealed opaque envelopes, which will be opened only when a patient is enrolled and meets all inclusion criteria. The principal doctor (CL) will assign the participant to a group on the basis of the number. The research assistant should receive the notification in a timely fashion and assign patients to their study group strictly as required. This study will be single-blind. The participants will be blinded to the allocation of the participants, whereas the investigators and project manager will be unblinded. If an unexpected emergency occurs, allocation will be disclosed to the investigators, the participant will be withdrawn from this study, and a detailed explanation will be recorded if unblinding happens.

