### Study dropouts

All recruited participants have the right to quit this study at any time for any reason based on the ethical consideration without any negative effects on their further therapy. Meanwhile, all researchers have the right to terminate the enrollment of any patients at any time within reasonable circumstances. All changes and reasons will be recorded immediately in the case report form (CRF). If the dropout rate is higher than 10%, we will apply multiple imputation to avoid pitfalls involved with listwise deletion of cases. The intention-to-treat principle will be applied to analyze the data.

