#### Primary and secondary outcomes

All outcomes will be defined in accordance with two previous studies [17, 18]. The primary outcomes are the levels of leukocytes, neutrophils, and inflammatory factors—interleukin-1β (IL-1β), IL-6, IL-8, IL-2, tumor necrosis factor-alpha (TNF-α), C-reactive protein (CRP), prostaglandin E_2_ (PGE_2_), and 5-hydroxytryptamine (5-HT)—on the first postoperative day. On the first postoperative morning, a trained nurse will collect blood samples and then send samples to test. The mean difference of the levels of leukocytes, neutrophils, and inflammatory factors will be compared between the two groups.

The secondary outcomes are (i) the levels of leukocytes, neutrophils, and inflammatory factors (IL-1β, IL-6, IL-8, IL-2, TNF-α, CRP, PGE_2_, and 5-HT) on the second and third postoperative days; (ii) the incidence of postoperative fever on the first, second, and third postoperative days; (iii) the volumes of chest drainage within the first 3 operative days, the duration of drainage, and postoperative hospitalization; and (iv) the incidence of postoperative complications (incision infection, pain, atelectasis, hemorrhage, etc.) and the incidence of pleural effusion requiring thoracic puncture or drainage within 30 days after surgery.

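### Three eligibility criteria can be judged only after randomisation, and one only after the lavage, so applying them as exclusions contradicts the stated intention-to-treat analysis

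*Protocol article*

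**What the plan says.** All references are to the protocol article.

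- **Time at which eligibility applies.** Inclusion criteria: "Patients who meet all the following criteria at the start of the treatment are eligible for this study". Exclusion criteria: "Patients who meet any of the following criteria at the start of treatment are excluded from this study".
- **Criteria that look forward from that time.** Inclusion (v) is "confirmed diagnosis of NSCLC through pathological examination after surgery". Exclusion (viii) covers intraoperative accidents: blood loss above 500 mL, conversion to open surgery or cardiac arrest. Exclusion (ix) is "patients with severe postoperative bleeding or persistent air leakage, which require reoperations".
- **Allocation.** Randomization and blinding: "Randomization of trial participants will be based on computer-generated random numbers prior to surgery". The envelopes are those "which will be opened only when a patient is enrolled and meets all inclusion criteria". Investigators are unblinded, and the Discussion adds that the surgeons cannot be blinded.
- **Intervention.** The lavage is given after hemostasis and before the chest is closed (Intervention, Group A).
- **Analysis.** Study dropouts: "The intention-to-treat principle will be applied to analyze the data".
- **Outcomes.** Hemorrhage is named among the postoperative complications that form a secondary outcome (Primary and secondary outcomes). The Complications section lists bleeding and prolonged air leak.

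**The concern.** A criterion that is judged after allocation removes a randomised patient. If that patient leaves the analysis, the comparison is no longer between the groups formed by randomisation. If the patient stays, the exclusion criterion has not been applied. The article states both rules and nowhere says which gives way.

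The three criteria carry different risks.

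- **Exclusion (ix)** comes after the lavage and could depend on its volume. It is also a severe form of events that the trial sets out to count. Excluding these patients takes the worst bleeding and air-leak cases out of the safety comparison. If a leak is declared persistent after the first-morning blood sample, a primary outcome that has already been measured is discarded as well.
- **Exclusion (viii)** concerns events that mostly precede the lavage, so the lavage cannot have caused them. The risk is that allocation may already be known to unblinded surgeons, which matters most for a discretionary decision such as conversion.
- **Inclusion (v)** should not depend on lavage volume. Removing these patients departs from intention-to-treat but is unlikely to bias the comparison. Its main harm is practical: an envelope that may be opened only when every inclusion criterion is met can never be opened in time for the lavage.

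The multiple imputation described under Study dropouts applies only above 10% dropout, so it would not protect against smaller, selective removals.

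**Working it through.** **1. Order of events.** Each criterion is set against the time at which it can be known.

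| Item | Known | Relative to preoperative allocation | Relative to lavage |
|---|---|---|---|
| Inclusion (v), pathology | After surgery | After | After |
| Exclusion (viii), intraoperative accident | During surgery | After | Mostly before |
| Exclusion (ix), reoperation | After surgery | After | After |

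If the envelopes are in fact opened in theatre just before lavage, (viii) moves to before allocation. Items (v) and (ix) do not move.

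**2. The plan's own power figure.** The inputs from Sample size are an effect size of 0.5, 200 per group, 10% dropout and a 5% type I error rate. Retained per group: 200 × (1 − 0.10) = 180. A two-sided two-sample t test (noncentral t) with 180 per group gives 99.72%, exactly the stated value. Two-sided testing is not stated but is what reproduces the figure.

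**3. Power under removal, same method.** 200 per group: 99.88%. 160 per group: 99.38%. 140 per group: 98.64%. Loss of power is therefore not the issue.

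**4. Possible bias in a day-1 marker.** The article gives no removal rates and no marker levels for removed patients, so everything in this step is assumed. Let there be no true difference between the arms. Let a share p of an arm be removed, and let the removed patients average d SD above their whole-arm mean. The retained mean is then −p·d/(1 − p), and the spurious difference between the arms is

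d × [p₂/(1 − p₂) − p₁/(1 − p₁)].

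- Equal removal (5% v 5%) with equal d: 0.
- 2% v 5%: 0.05/0.95 − 0.02/0.98 = 0.0526 − 0.0204 = 0.0322. With d = 1 this is 0.032 SD. With d = 1.5 it is 0.048 SD. Divided by the planned 0.5 SD, these are about 6% and 10%.
- Test size for 2% v 5%: 196 and 190 patients are retained, so SE = √(1/196 + 1/190) = 0.102. By normal approximation the nominal 5% becomes 6.2% (d = 1) or 7.6% (d = 1.5). Over d = 0.5 to 2 the range is 5.3% to 9.7%.
- If d is measured from the retained patients instead of the whole-arm mean, the difference is d × (0.05 − 0.02) = 0.030 to 0.045 SD, much the same.

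**5. Possible loss of safety events.** Under the same assumed rates for (ix), 2% of 200 = 4 and 5% of 200 = 10 reoperations would occur. With (ix) applied, both arms would show 0.

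**The case against.** Several points can fairly be made for the plan.

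- **The timing wording is loose.** The phrase placing randomisation before surgery may describe only the generation of the numbers, with envelopes opened in theatre. No time of opening is given. It would therefore be too strong to infer that the surgeon certainly knows the arm when an intraoperative accident is judged. This stands, and it could rescue (viii). It cannot rescue (v) or (ix), which follow the lavage on any reading.
- **The criteria are not equally dangerous.** A reader might infer that all three remove patients because of the intervention. Only (ix) can. The accidents in (viii) mostly precede the lavage, and histology should not respond to it.
- **The bias may be small or absent.** A reader might infer that the removed patients are those with the largest inflammatory response, or that the distortion takes up a large share of the planned effect. The article gives no marker levels for such patients and no removal rates, so neither inference is supported.
- **Events are recorded.** All adverse events go into the case report form, reasons for changes are recorded, and bleeding or air leak that does not need reoperation still counts. This helps, but nothing says that excluded patients enter the comparison between arms.
- **A separate analysis plan may define the analysis sets.** It may. The conflict is nevertheless between rules that the article itself states. A plan that applied the exclusions after randomisation would breach intention-to-treat, and one that kept everyone would override the exclusions.

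**Conclusion.** The contradiction holds on the text alone and needs no calculation. The timing of eligibility, the envelope rule, the three late criteria and the intention-to-treat statement cannot all be followed. Exclusion (ix) is sufficient by itself to require a change, because it conditions on a post-lavage event that is a severe form of a secondary outcome (hemorrhage) or of a listed complication (air leak). Exclusion (viii) is a risk only so far as allocation is known before those events. Inclusion (v) is mainly a rule that cannot be carried out.

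The size of any bias is unknown. It is nil under equal removal with equal shifts, and about 0.03 to 0.05 SD under an assumed 2% v 5% removal with removed patients 1 to 1.5 SD above their whole-arm mean. The effect on the safety comparison is more direct, since every reoperation for bleeding or persistent air leak would drop out of it. The stated power of 99.72% is correct and is not materially affected.

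**What to change.** 1. Delete (ix) as an exclusion. Keep these patients in the analysis and report reoperation for bleeding or air leak as complications by arm.
2. State that the envelope is opened in theatre after hemostasis and immediately before lavage, once the events in (viii) up to that point have been ruled out. Exclusion (viii) then becomes a true pre-randomisation criterion.
3. Reword (v) as confirmed or clinically suspected NSCLC at randomisation, so that the envelope rule can be followed. Analyse all randomised patients and show the pathology-confirmed subset as a sensitivity analysis. If the investigators prefer a pathology-confirmed main population, they should name it as a modified population and report removals by arm.

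The cost is a protocol amendment, which Protocol amendments provides for and which can be made before patients enter, since Trial status says recruitment has not opened. The same envelopes are used, only opened later. Power does not suffer: it is 99.88% with all 200 per group analysed. The real downside is some dilution of the target population by patients who prove not to have NSCLC, of a size that the article does not give.

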### Randomization and blinding

Randomization of trial participants will be based on computer-generated random numbers prior to surgery. The random numbers will be printed and placed in consecutively numbered and separate sealed opaque envelopes, which will be opened only when a patient is enrolled and meets all inclusion criteria. The principal doctor (CL) will assign the participant to a group on the basis of the number. The research assistant should receive the notification in a timely fashion and assign patients to their study group strictly as required. This study will be single-blind. The participants will be blinded to the allocation of the participants, whereas the investigators and project manager will be unblinded. If an unexpected emergency occurs, allocation will be disclosed to the investigators, the participant will be withdrawn from this study, and a detailed explanation will be recorded if unblinding happens.

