#### Group A (experimental group): 500 mL pleural lavage fluid

Before closing the chest wall, we will perform careful hemostasis and then flush the thoracic cavity with 500 mL 0.9% sodium chloride injection at 38–40 °C. A 28-F catheter will be indwelled for chest drainage.

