## Discussion

It is essential to flush the thoracic cavity before chest wall closure. However, scant data could be found in the literature. The most frequently used method is to flush the thoracic cavity with 0.9% sodium chloride injection heated nearly to the temperature of the human body at 38~40 °C. No determinant criteria on volume of pleural lavage fluid have been built. If the volume of pleural lavage is too small, the residual tumor cells and tissue cannot be washed away, which may result in increased absorption of inflammatory mediators, fever, and even severe inflammatory reactions and will affect prognosis and prolong hospital stay. Furthermore, the residual tumor cells may increase the risk of recurrence and metastasis. If the volume of pleural lavage is too high, it will cause waste of resources and prolongation of operation time.

The study will enroll 400 NSCLC patients undergoing VATS lobectomy and MLND and divide them into two groups. This study aims to find out whether different volumes of pleural lavage fluid (0.9% sodium chloride injection) have different effects on prognosis of NSCLC patients measuring by some important clinical indices such as the plasma levels of leukocytes, neutrophils, inflammatory factors, and the incidence of fever after operation were observed 1 to 3 days after operation.

However, the study has some limitations. First, it is a single-center trial, which will restrict its generalizability, so a multiple-center large-sample clinical trial is warranted in the future. Second, the anesthesiologist and surgeons in charge of the intraoperative part of the study cannot be blinded to this study group regarding the safety. Third, the hospitalization time may be different across participants, which may bring effects on the prognosis of patients with NSCLC. Fourth, larger patients may need different volumes of pleural lavage.

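### Randomisation is placed before surgery and nothing withholds the lavage volume from the surgeon until it is needed, which leaves an avoidable risk of performance bias in the earlier operative steps

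*Protocol article*

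**What the plan says.** **Timing of allocation.** Randomization and blinding says: "Randomization of trial participants will be based on computer-generated random numbers prior to surgery". The numbers are held in sealed, numbered, opaque envelopes, "which will be opened only when a patient is enrolled and meets all inclusion criteria". The principal doctor "will assign the participant to a group on the basis of the number", and a research assistant is notified.

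**Who knows the arm.** Participants are blinded, "whereas the investigators and project manager will be unblinded". The Discussion gives as a limitation that "the anesthesiologist and surgeons in charge of the intraoperative part of the study cannot be blinded to this study group regarding the safety". Laboratory technicians (Data collection and outcomes) and the two statisticians (Statistical analysis) are blinded.

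**Where the arms diverge.** For group A: "Before closing the chest wall, we will perform careful hemostasis and then flush the thoracic cavity with 500 mL". Group B receives 3000 mL, with everything else as in group A. The volume is therefore the only planned difference, and it first applies after haemostasis.

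**Related rules.** Exclusion criterion (viii) removes patients with intraoperative events: blood loss above 500 mL, conversion to an open procedure, or cardiac arrest. Inclusion criterion (v) requires "confirmed diagnosis of NSCLC through pathological examination after surgery".

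**The concern.** A comparison of two rinse volumes is clean only if everything before the rinse is done in the same way in both arms. The surest protection is that the operator does not know the arm while doing it. Here that protection is available, because the volume is not needed until haemostasis is finished, but the article does not use it.

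The article also supplies a reason why knowledge could matter. Background and Discussion both argue that too small a rinse leaves residual cells and tissue, with more absorption of inflammatory mediators and fever. A surgeon who shares that view and knows that 500 mL is coming could suction, coagulate or inspect more thoroughly, or do less of this when 3000 mL is coming. Tissue trauma and residual blood plausibly affect day-1 leukocytes and inflammatory markers (primary outcomes) and drainage and haemorrhage (secondary outcomes). A difference made in this way sits in patients who stay in every analysis. Blinded laboratory staff, blinded statisticians and the intention-to-treat principle cannot remove it.

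There is a second consequence. If allocation precedes surgery, the events in exclusion (viii) occur after randomisation. The decision to convert and the estimate of blood loss are partly the surgeon's own, so an unblinded surgeon can influence who is removed from each arm.

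**Working it through.** **1. Order of events, with the passages side by side.**

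| Step | Source | Could the surgeon know the arm? |
|---|---|---|
| Randomisation before surgery; principal doctor assigns; investigators unblinded | Randomization and blinding | Yes; no rule against it |
| Lobectomy, node dissection | Trial procedure | Yes; no rule against it |
| Intraoperative exclusions (viii) | Exclusion criteria | Yes; no rule against it |
| Haemostasis | Group A | Yes; no rule against it |
| Lavage, 500 or 3000 mL | Groups A and B | Unavoidable |
| Closure | Groups A and B | Unavoidable |
| Pathology confirms NSCLC | Inclusion criterion (v) | Known only after surgery |

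Knowledge of the arm is unavoidable only from the lavage onward.

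**2. The opening condition.** The envelope is to be opened only once all inclusion criteria are met, but criterion (v) is postoperative pathology. Read literally, the envelope could be opened neither before surgery nor before the lavage, so the trial could not run. Some earlier opening must be intended. The phrase placing randomisation before surgery points to a preoperative one, but no time of opening is given.

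**3. The plan's own figure.** Inputs from Sample size: effect size d = 0.5, type I error 5%, 200 per arm, 10% dropout.

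- n per arm = 200 × 0.9 = 180; df = 2 × 180 − 2 = 358.
- Noncentrality = d × √(n/2) = 0.5 × √90 = 4.74.
- Two-sided power from the noncentral t distribution = 99.72%.

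This matches the stated 99.72%.

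**4. Sensitivity to a bias (illustration).** The documents give no size for any surgeon effect. Assume that lavage has no effect and that arm-dependent surgery shifts mean day-1 leukocytes by b SD. The probability of a significant result uses the same formula with b in place of d.

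| Assumed b (SD) | Noncentrality b × √90 | Probability of P < 0.05, 180 per arm |
|---|---|---|
| 0 | 0 | 5% |
| 0.05 | 0.47 | 7.6% |
| 0.1 | 0.95 | 15.7% |
| 0.2 | 1.90 | 47.3% |
| 0.3 | 2.85 | 81.0% |

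These rows show only that a trial this well powered is also sensitive to small biases from any cause. They are no evidence that such a bias will occur. A shift opposite to a true effect would hide it.

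**5. Effect of delayed opening.** It enters none of the inputs in step 3: 400 participants, power 99.72%.

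**The case against.** The strongest case on the other side has five parts.

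- **The timing is inferred.** The article does not say that the envelope is opened before incision. The words about surgery attach to randomisation, and the opening has its own condition, with no clock time. All thoracic surgeons in the department are informed of the trial (Recruitment of participants), so the operator need not be the doctor who allocates. The text on blinding is also unsettled: investigators are unblinded, yet an emergency is said to disclose the allocation to them. This stands. A reader might infer that the surgeon knows the volume throughout the operation, but the article does not state that.
- **The Discussion names persons, not a period.** It says which people cannot be blinded, and does not say that they know the arm throughout the operation. This stands. The limitation is openly disclosed, with safety as the reason. However, the article does not explain why safety requires knowledge of the volume before the lavage.
- **The mechanism is conjecture.** Careful haemostasis and otherwise identical procedures are prescribed, both arms are labelled experimental, and the article names drawbacks of both too little and too much fluid. No surgeon preference is documented. This stands: the mechanism is plausible but not shown. A prescription of equal care is still weaker protection than not knowing the arm.
- **The percentages rest on assumed shifts.** This stands. The largest, 0.3 SD, is 0.3/0.5 = 60% of the whole effect that the plan expects.
- **Moving the time of opening alone would not be enough.** The all-inclusion-criteria condition would still be breached because of criterion (v). This stands, and the fix has to deal with it.

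None of these points shows a safeguard that withholds the volume until it is needed.

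**Conclusion.** The point holds as an avoidable risk of performance bias. It rests on the natural reading of Randomization and blinding: allocation before surgery, with no rule that keeps it from the operator. On that reading, lobectomy, node dissection and haemostasis may be done with the arm known, although the arms differ only at the lavage that follows. The day-1 inflammatory, drainage and bleeding outcomes are exposed.

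The size and direction of any bias are unknown. A reader might take the rejection rates of 16% to 81% as an estimate of false-positive risk in this trial. They are not: they follow wholly from assumed shifts of 0.1 to 0.3 SD. The documents also do not support a claim that surgeons will behave differently by arm.

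The consequence for exclusion (viii) depends only on allocation preceding surgery, which the article states: those exclusions become post-randomisation exclusions. That an unblinded surgeon could influence them rests on the same reading as above. This is a worthwhile and cheap improvement to a design choice, and does not invalidate the trial.

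**What to change.** Three linked edits, feasible because Trial status says that recruitment has not opened:

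1. **Randomization and blinding, timing.** State that the numbered envelope stays sealed until the surgeon declares resection, node dissection and haemostasis complete. It is then opened in theatre by existing staff, such as the research assistant or circulating nurse, who announces the volume.
2. **Randomization and blinding, opening condition.** Replace the requirement that all inclusion criteria be met with the eligibility criteria that can be assessed by that moment, and reconcile this with inclusion criterion (v), which depends on postoperative pathology. Most events under exclusion (viii) would then occur before allocation and would no longer be post-randomisation exclusions.
3. **Discussion.** Limit the statement on surgeon unblinding to lavage and closure.

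Cost: the envelope must be in theatre, and warmed saline for the larger volume must be ready in every case. Sample size, power and treatment in either arm are unchanged. Exclusion (ix) and pathology under criterion (v) would still fall after allocation, so delayed opening does not settle how those patients are handled.
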